## Abstract

**Background:**

Despite several attempts to improve the durability of the reconstruction of paraesophageal hernias (PEH), recurrence rates remain high. Gastropexy has often been added to the reconstruction with the intention to reduce recurrence rates by anchoring the stomach in the abdominal cavity. The efficacy of adding gastropexy to standard PEH repair has, however, not yet been investigated in a randomized controlled trial setting.

**Methods:**

All patients scheduled for PEH repair are assessed for eligibility for enrolment. Preoperative work-up includes upper GI endoscopy, computed tomography, and symptom assessments. Participants will be randomized (1:1) to either the control or intervention group. In the control group, patients will have a standardized repair, including posterior crural repair and a total fundoplication. In the intervention group, a three-point gastropexy using running non-absorbable sutures will be added to the same reconstruction as in the control group: a posterior fixation of the wrap to the diaphragm, a lateral fixation of the left wrap to the diaphragm, and an anterior fixation of the minor curvature to the inner surface of the anterior abdominal wall. The primary outcome is computed tomography-verified radiological recurrence at 1 year. Secondary outcomes include radiological recurrence at 3 years, patient-reported quality of life, and disease-specific symptoms at 3 months, 1 year, and 3 years, as well as postoperative complications. The study design is double-blinded, with both participants and outcome assessors being blinded to the allocation of patients to treatment arms.

**Discussion:**

Although gastropexy is frequently used in PEH repair with the intent to reduce recurrence rates, the scientific evidence behind its effects is limited. The present trial is the first RCT to evaluate the efficacy of gastropexy combined with a standardized PEH repair.

**Trial registration:**

The trial is registered at ClinicalTrials.gov, NCT06107634. Registered 9 September 2023.

**Supplementary Information:**

The online version contains supplementary material available at 10.1186/s13063-026-09578-7.

## Administrative information

Note: the numbers in curly brackets in this protocol refer to SPIRIT checklist item numbers. The order of the items has been modified to group similar items (see http://www.equator-network.org/reporting-guidelines/spirit-2013-statement-defining-standard-protocol-items-for-clinical-trials/).

## Introduction

### Background and rationale {6a}

Paraesophageal hernias (PEH) constitute a subtype of hiatal hernias in which large parts of, or the entire stomach, with or without other abdominal viscera, have migrated into the chest cavity through a dilated diaphragmatic hiatus. The prevalence of PEH has been reported to be approximately 3% in middle-aged and older adults, increasing with advancing age [1]. While some PEHs are asymptomatic, others present with a wide range of symptoms including chest or abdominal pain, dysphagia, dyspnea, indigestion, or gastroesophageal reflux (GERD). In severe cases, PEH may also lead to life-threatening complications including volvulus, incarceration, strangulation, or perforation [2–4].

The indication for surgical repair remains controversial. Some suggest that all patients with PEH should undergo surgical repair to avoid acute complications, while many experts argue that only symptomatic hernias should be considered for repair [4–10].

GERD is reported in 30–50% of patients with PEH and can also develop after surgical repair in previously asymptomatic patients. Therefore, the surgical reconstructive procedures should aim not only to restore the anatomy of the diaphragmatic hiatus, remove the hernia sac, and reduce the hiatal opening by adapting the crurae. It should also include an anti-reflux procedure—most commonly a total (Nissen) fundoplication [11–13].

Despite several technical refinements, reported recurrence rates following PEH repair remain high, ranging from 7 to 66% [11, 14–20]. A challenge in PEH repair is that the hiatal reconstruction is exposed to unfavorable physical and functional counteracting forces, promoting both the occurrence and recurrence of PEH, not least due to the significant pressure gradients between the abdominal and thoracic cavities. Coughing, sneezing, vomiting, and heavy lifting are believed to be important factors causing PEH recurrence [21]. Another factor believed to contribute to the high recurrence rates is that the esophagus is permanently attached proximally at the pharyngoesophageal junction and, through its muscular activity, repetitively and forcefully pulls the gastroesophageal junction (GEJ) and the upper part of the stomach in an oral direction.

To prevent recurrence following PEH repair, several surgical techniques have been developed. Among these, procedures in which the stomach is anchored in the abdominal cavity and to the diaphragm by sutures (gastropexy) are among the most commonly practiced [22, 23]. Although the addition of gastropexy to standard PEH repair has garnered widespread clinical attention, evidence supporting its efficacy remains limited [24–28].

### Objectives {7}

The primary objective of this trial is to evaluate if the addition of gastropexy can reduce hiatal hernia recurrence rates at 1 year following PEH repair, compared to crural repair with a total (Nissen) fundoplication alone.

Secondary objectives are to assess if, and if so, how the addition of gastropexy affects the following:Recurrence rates at 3 yearsPatient-reported quality of lifePatient-reported disease-specific symptomsRates and severity of postoperative complications

### Trial design {8}

This study is a randomized, multicenter trial comparing a standardized PEH repair, with or without the addition of gastropexy. The trial design is a parallel group study with block randomization and a 1:1 allocation ratio. The primary objective is to evaluate superiority with the hypothesis that the addition of gastropexy reduces the recurrence rate of radiologically verified hiatal hernia recurrence at 1 year postoperatively.

## Methods: participants, interventions, and outcomes

### Study setting {9}

A nationwide study with six centers in Sweden participating. All procedures will be performed or supervised by an experienced upper gastrointestinal surgeon who has performed more than 25 PEH repairs.

### Eligibility criteria {10}

All individuals aged 18 years or older scheduled for repair of a hiatal hernia grades II–IV (PEH) at participating sites will be considered for entry. Patients will be excluded if they:Have undergone previous surgery involving the stomach or the gastroesophageal junction,Have achalasia or other major esophageal motility disorders,Are unable to understand the purpose of the study and/or are unwilling to give informed consent orHave severe comorbidities (defined by the American Society of Anesthesiologists (ASA) physical status score of more than III).

### Who will take informed consent? {26a}

Either a trained research nurse or a surgeon will introduce and explain the purpose and nature of the trial to all patients, providing them with written information about the study. After reviewing the information, patients will have the opportunity to engage in informed discussions with the research nurse or surgeon. Following this discussion, written informed consent will be obtained from all patients who agree to participate in the study.

### Additional consent provisions for collection and use of participant data and biological specimens {26b}

No ancillary studies are currently planned. Any future use of data collected in the present trial for ancillary research will require separate approval from the national ethics review board. Additional participant consent will be obtained if deemed necessary by the ethics authority.

## Interventions

### Explanation for the choice of comparators {6b}

While there are several controversies and no consensus regarding the optimal surgical treatment for paraesophageal hernias, most agree that the standard procedure should include a full mediastinal dissection with adequate esophageal mobilization and complete resection of the hernia sac. In addition, crural repair and an anti-reflux procedure are strongly recommended [6, 8, 9]. The type of fundoplication may affect the risk of postoperative symptoms, such as reflux, bloating, and dysphagia [29, 30]. To ensure standardization, we have chosen to incorporate a total (Nissen) fundoplication, as this technique is the most widely used and recognized worldwide [11].

### Intervention description {11a}

All surgeries will be performed under general anesthesia. The method used for abdominal entry, port placement, and type of liver retractor is at the surgeon’s discretion. Ultrasonic shears are used for dissection. The herniated viscera are completely reduced into the abdomen, and the hernia sac is fully dissected and resected. The esophagus is mobilized intraabdominally until at least 3 cm rests independently below the hiatus without tension. Effort is made to identify and preserve the anterior and posterior vagal nerves. A posterior crural closure with running non-absorbable sutures is performed. An additional anterior crural closure may be performed at the surgeon’s discretion. The fundus is mobilized to allow a floppy fundoplication. A total fundoplication is created by three interrupted non-absorbable sutures [31–33]. No bougies are used routinely for calibration of the fundoplication.

In the intervention group, in addition to the above, a three-point gastropexy is performed (Fig. 1). First, the right fundus flap is adapted posteriorly to the crural portion of the diaphragm with a 2–3 cm long running non-absorbable suture (“posterior gastropexy”). Second, the left fundus flap is adapted to the diaphragm anterolateral to the hiatus with a 2–3 cm long running non-absorbable suture (“left lateral gastropexy”). Finally, the minor curvature of the anterior stomach wall is adapted during reduced intraabdominal pressure to the anterior abdominal wall with a 2–3 cm long running non-absorbable suture (“anterior gastropexy”).

**Fig. 1 Fig1:**
[figure not shown]
Schematic illustration of the positioning of the gastropexy sutures. (**A**) Posterior gastropexy, (**B**) left lateral gastropexy, and (**C**) anterior gastropexy. The anterior gastropexy is shown before tightening to improve visualization of the planned fixation points

### Criteria for discontinuing or modifying allocated interventions {11b}

If the surgeon deems it necessary to add adjunct procedures or deviate from the protocol in any other way, this is noted in the operative case report form as well as in the medical record.

### Strategies to improve adherence to interventions {11c}

Before the start of the trial, surgical techniques will be standardized and harmonized across the participating sites. A video demonstrating the proper technique for the intervention will be provided to all sites. Each site is required to submit a video illustrating the procedure as performed at the respective center. These videos will be reviewed by the trial steering committee to verify adherence to the standardized surgical techniques before commencement of operating patients within the study, with particular focus on gastropexy techniques, especially anterior gastropexy, including confirmation of anatomical landmarks, fixation points, and suture placement to ensure procedural standardization across centers.

### Relevant concomitant care permitted or prohibited during the trial {11d}

The PEH repair must strictly adhere to the study protocol to ensure consistency across centers. However, there are no restrictions on perioperative or other medical care outside the scope of the protocol.

### Provisions for post-trial care {30}

Healthcare in Sweden is publicly funded. Post-trial care will be provided by the referring or operating hospital. In case of harm, any compensation needed is provided by the Swedish patient insurance system.

### Outcomes {12}

#### Primary outcome measure

Difference between the groups in the rate of participants with radiologically verified recurrence at 1 year after surgery. Recurrence is defined as any part of the stomach or other abdominal viscera located above the diaphragm at computed tomography (CT).

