### Sample size {14}

Previous studies have suggested recurrence rates after paraesophageal hernia repair ranging from 7 to 66% [15–20]. We have estimated the recurrence rate to be 30% in the control group and hypothesize that this can be reduced to 10% with the addition of gastropexy. With an α of 0.05 and a power of 80% (β = 0.2), we calculate a required sample size of 62 participants per arm, yielding a total of 124 evaluable participants. To account for an estimated 15% loss to follow-up, based upon previous studies with similar follow-up at the same institution, we aim to include 150 participants. The primary analysis will use multiple imputation under a missing-at-random assumption to include all randomized participants; this approach is expected to preserve the planned power under the anticipated missingness.$$\begin{aligned}n&=\left[\sqrt{\frac{\left(0.3+0.1\right)}{2}\left(1-\frac{\left(0.3+0.1\right)}{2}\right)\left(1+\frac{1}{1}\right)}\ 1.96\ \right.\\&\left.+\ \sqrt{0.3\left(1-0.3\right)+\frac{0.1\left(1-0.1\right)}{1}}0.84\right]^{2}/{0.2}^{2}\approx 62\end{aligned}$$

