## Statistical methods

### Statistical methods for primary and secondary outcomes {20a}

Analyses will be performed on an intention-to-treat basis. Descriptive statistics will be used to present overall and group-wise data.

The primary outcome will be analyzed using logistic regression with treatment group as the main independent variable, with pre-specified co-variates including age, BMI, and hiatal area.

Secondary categorical outcomes will be analyzed using logistic regression and continuous outcomes using linear regression. Continuous outcomes with repeated measurement will be analyzed using linear mixed-effect models.

Exploratory post hoc analyses will assess the association between surgeon experience, defined as the number of prior paraesophageal hernia repairs performed, and primary and secondary outcomes.

All analyses will be performed using R Statistical Software (version 4.4.1, 2024–06–14, R Core Team, Vienna, Austria).

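### The primary outcome is a difference in 1-year recurrence rates, but the stated adjusted logistic analysis gives a conditional log odds ratio directly, with no stated step back to that difference

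*Protocol article*

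**What the plan says.** Under Primary outcome measure, the quantity of interest is "Difference between the groups in the rate of participants with radiologically verified recurrence at 1 year after surgery". Sample size {14} works on the same scale: "We have estimated the recurrence rate to be 30% in the control group", with a hoped-for fall to 10%, and its formula divides by the square of 0.2, the difference between the two proportions. The result is given as "With an α of 0.05 and a power of 80% (β = 0.2), we calculate a required sample size of 62 participants per arm".

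Statistical methods {20a} names one primary analysis: "The primary outcome will be analyzed using logistic regression with treatment group as the main independent variable". The model is adjusted, and the covariates it lists are age, BMI and hiatal area. Section {20c} adds multiple imputation by chained equations, with the planned regression run in each imputed dataset and the estimates combined by Rubin's rules. Sample size {14} says that imputation serves to keep everyone randomised in the primary analysis.

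The protocol names no effect measure for reporting: odds ratio, risk ratio and risk difference are all absent as terms. It does not mention standardised or marginal risks. Section {20a} does promise descriptive statistics by group.

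**The concern.** The protocol fixes the outcome measure, model, covariates, imputation method and pooling rule. Followed as written, that sequence ends at a pooled treatment coefficient, which is a log odds ratio conditional on the covariates. The outcome measure is a difference in rates. At the planned rates recurrence is common in the control arm, so the odds ratio is not a close stand-in for the risk ratio, and neither of them is the difference.

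Two things are at stake. First, the absolute reduction in recurrence is what the protocol sets out to measure, yet it has no stated adjusted estimate or interval on the full randomised set. The descriptive rates by arm are not stated to be adjusted or to use the imputed data, so they could disagree with the primary analysis. Second, with no effect measure named, the choice between scales could be made after the results are seen.

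**Working it through.** **Inputs.** From Sample size {14}: recurrence 30% (control) and 10% (gastropexy), α 0.05 (two-sided, from the 1.96 in the formula), power 80%, loss 15%, target 150, cited range of recurrence 7% to 66%. From Trial design {8}: 1:1 allocation. From {20a}: covariates age, BMI and hiatal area. Their prognostic strength is not given, so it is assumed below and shown as a range.

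**1. The plan's own figure.** n = [1.96 × √(2 × 0.2 × 0.8) + 0.84 × √(0.3 × 0.7 + 0.1 × 0.9)]² / 0.2²
= [1.96 × 0.5657 + 0.84 × 0.5477]² / 0.04
= (1.1087 + 0.4601)² / 0.04 = 61.5, rounded up to 62 per arm. This reproduces. Power at 62 per arm is 80.3%. Inflation gives 124 / 0.85 = 145.9, so 146, which 150 covers.

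**2. The planned effect on each scale.**
- Risk difference: 0.10 − 0.30 = −0.20
- Risk ratio: 0.10 / 0.30 = 0.33 (a 67% fall in risk)
- Marginal odds ratio: (0.10/0.90) / (0.30/0.70) = 0.259 (a 74% fall in odds)

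**3. The odds ratio after adjustment.** Let the covariates contribute s·X to the log odds, with X standard normal. Solve for a and β so that the average of expit(a + sX) is 0.30 and the average of expit(a + β + sX) is 0.10. The conditional odds ratio is exp(β). In every row the marginal risks are 30% and 10%, so the risk difference stays at −20 points.

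| Assumed SD s | Conditional odds ratio |
|---|---|
| 0 | 0.259 |
| 0.25 | 0.256 |
| 0.5 | 0.247 |
| 0.75 | 0.232 |
| 1.0 | 0.213 |
| 1.5 | 0.171 |

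**4. What a single odds ratio says about the difference.** With control risk p, the treated risk is q = o/(1 + o), where o = 0.259 × p/(1 − p). At p = 7%, q = 1.9% and the difference is about −5 points. At 30%, q = 10% and it is −20. At 66%, q = 33.5% and it is about −33. Over the range of recurrence that the protocol cites, the odds ratio alone does not fix the outcome measure.

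**5. Can the same model deliver the difference?** Set every participant to gastropexy, then every participant to control, average the predicted risks, and subtract. In 2,000 simulated trials of 62 per arm, with three normal covariates and complete data:

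| Assumed SD | Mean standardised risk difference (empirical SE) | Power, adjusted logistic Wald test | Power, two-proportion z-test |
|---|---|---|---|
| 0 | −0.200 (0.070) | 80.8% | 81.8% |
| 0.5 | −0.199 (0.069) | 81.4% | 80.8% |
| 1.0 | −0.201 (0.067) | 84.4% | 79.9% |

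The model recovers the planned difference, and the logistic test costs no material power. The simulation did not include missing data or imputation.

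**The case against.** The best defence is that no section mentions an odds ratio. Section {20a} names a model, and {20c} says that estimates are pooled without limiting these to coefficients. A standardised risk difference is itself an estimate from a logistic model. A reader might infer that the plan can yield, or will report, only an odds ratio; the text does not support that. What stands against this defence is that a fitted logistic model gives a log odds ratio directly, and the further step to the defined quantity is not stated.

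The wording could also be generic. The secondary outcomes are all introduced as between-group differences, including hernia type and complication severity, where subtraction has no meaning. But the primary measure is a difference in a rate, and the sample size is computed on that scale.

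An analysis plan that is not shown may name the measure. That would settle the matter in practice, and for this reason the point is a mismatch to reconcile and no proof of a flawed analysis. The descriptive rates by arm will also give readers some view of the absolute effect, though not one stated to match the primary analysis.

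Three stronger inferences fail. The sample size is not on the wrong footing: 62 per arm reproduces, and sizing on two proportions and then testing with a logistic model addresses the same null hypothesis. The test is not invalid or short of power. And adjustment does not bias the odds ratio: its shift is a property of that measure, most of the distance from the risk ratio (0.33 to 0.26) comes from the odds scale itself, and the rest depends on covariate strength that the protocol does not give.

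**Conclusion.** The point holds as a mismatch between the defined outcome measure and the direct output of the stated analysis. It affects how the effect is estimated and reported, and leaves the design and the test as they are. At the planned rates the same effect reads as −20 points, a risk ratio of 0.33 or a marginal odds ratio of 0.26. The additional movement from adjustment is small at an assumed SD of 0.5 (0.259 to 0.247) and clearer only with strongly prognostic covariates (0.213 at 1.0). These conditional figures rest on a normally distributed linear predictor with assumed SD; the other figures follow from the protocol's own rates. The change should be made, because it is nearly free and delivers the quantity the protocol defines, with an interval, on everyone randomised.

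**What to change.** Keep the adjusted logistic model and the imputation. In each imputed dataset, compute the standardised (marginal) risk in each arm by averaging predicted risks over all participants, take the risk difference, and obtain its standard error by the delta method or bootstrap. Pool by Rubin's rules. State in {20a} that this risk difference with its 95% CI is the primary effect estimate and that the adjusted odds ratio is supportive.

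The cost is about two sentences of text and a few lines of R. Data, model and sample size stay the same. Recruitment is expected to run to the end of 2026 and no interim analysis is planned, so the change can be made before the primary analysis.

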## Data collection and management

### Plans for assessment and collection of outcomes {18a}

Participants will undergo a study-specific low-dose CT scan of the upper abdomen and lower thoracic cavity at 1 and 3 years, with a permissible variation of ± 3 months from the specified time points. The CT protocol can be found in Supplement A. If a participant undergoes a clinically indicated CT scan that includes the upper abdomen and lower thoracic cavity within the specified time frame, the study-specific CT scan may be omitted. The CT scans will be reviewed by a specialized radiologist, blinded to the participants’ group allocation, to assess for recurrence.

Postoperative data including length of stay, complications, and reoperations will be collected by a research nurse or research fellow 30 days postoperatively. Severity of complications is graded according to the Clavien Dindo classification [34].

Patient-reported outcome measures (PROMs), including quality of life and the severity and frequency of symptoms, will be assessed at baseline, 3 months, 1 year, and 3 years. Health-related quality of life will be assessed with the Swedish version of the Short Form-36 (SF-36) questionnaire (RAND Corporation). SF-36 consists of 36 items grouped in eight domains, which can be summarized to mental and physical component scores [39–42].

The Gastrointestinal symptom rating scale (GSRS) measures symptoms of reflux, abdominal pain, indigestion, diarrhea, and constipation. The questionnaire consists of 15 items and uses a 7-point Likert scale, with 1 representing no symptoms and 7 representing severe symptoms. Scores are summarized for each of the five domains [38, 39].

The Dakkak dysphagia score assesses dysphagia. Participants report frequency (never, sometimes, or always) of dysphagia when eating nine types of solid, mashed, and liquid food. The generated score ranges from 0 to 45, where we will reverse the original scoring as done in previous studies, so that a higher score indicates more severe dysphagia [36, 37].

Additionally, a specific questionnaire will be used to assess the frequency of specific symptoms of heartburn, reflux, chest pain, dysphagia, globus sensation, respiratory symptoms, nightly cough, odynophagia as well as difficulty vomiting or belching.

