### Methods in analysis to handle protocol non-adherence and any statistical methods to handle missing data {20c}

With the randomization and intervention taking place in the operating room, we expect no protocol non-adherence. Prior to surgery, we will ensure that all preoperative questionnaires are completed, which should reduce the risk of missing baseline data. We will handle missing primary outcome data using multiple imputation by chained equations (MICE) under a missing-at-random assumption. The imputation model will include treatment group and pre-specified prognostic variables (including baseline characteristics and any available intermediate/follow-up measurements) to generate m imputed datasets; each dataset will be analyzed using the planned regression model for the dichotomous outcome (e.g., logistic regression), and estimates will be combined using Rubin’s rules.

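### Primary recurrence is the state of the hiatus on one CT at 1 year ± 3 months, so a recurrence re-repaired before that scan and intact on it is scored as no recurrence

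*Protocol article*

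**What the plan says.** - **Outcome.** Under Primary outcome measure, the outcome is "Difference between the groups in the rate of participants with radiologically verified recurrence at 1 year after surgery". Recurrence is purely a CT finding, with no operative or clinical component: "Recurrence is defined as any part of the stomach or other abdominal viscera located above the diaphragm at computed tomography (CT".
- **Timing.** Plans for assessment and collection of outcomes {18a} schedules a "study-specific low-dose CT scan of the upper abdomen and lower thoracic cavity at 1 and 3 years", with a tolerance of 3 months either side. The primary scan therefore falls in months 9 to 15 and is read by a blinded radiologist.
- **Other scans.** A clinically indicated CT can stand in for the study scan only if it is done "within the specified time frame, the study-specific CT scan may be omitted". Nothing is said about a recurrence seen on an earlier CT.
- **Reoperations.** The same section states: "Postoperative data including length of stay, complications, and reoperations will be collected by a research nurse or research fellow 30 days postoperatively". It describes no later collection.
- **Analysis.** Under {20a}, "Analyses will be performed on an intention-to-treat basis". Under {20c}, "We will handle missing primary outcome data using multiple imputation by chained equations (MICE) under a missing-at-random assumption". Sample size {14} adds that imputation is meant to bring every randomized participant into the primary analysis.
- **Three years.** The secondary recurrence outcome at 3 years uses the same CT-based approach.

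**The concern.** Objectives {7} and Trial design {8} ask whether adding gastropexy to the index repair lowers recurrence. A participant who recurs at, say, month 4, is reoperated and is scanned at month 12 contributes a scan of the second operation. If that second repair is intact, the record shows no recurrence in the randomized arm. The article does not describe how a re-repair is to be done, so the scan need not reflect the allocated technique at all.

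Recurrences that lead to early reoperation are plausibly among the more serious failures, and they are the ones this definition can turn into successes. If they cluster in the control arm, the benefit of gastropexy is understated. If they cluster in the gastropexy arm, its benefit is overstated and its failures are hidden. The 3-year outcome has the same gap over a longer exposure.

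**Working it through.** **Step 1: follow the text for four participants.**

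| Course | Result under the article |
|---|---|
| Recurrence, no reoperation, CT at 12 months | Recurrence, provided it is still visible (correct) |
| Recurrence on a clinical CT inside months 9–15, then re-repair | That CT may serve as the outcome scan, so recurrence can be counted |
| Recurrence and re-repair before month 9, intact on CT at 12 months | No recurrence. The outcome is observed, so imputation does not apply |
| Recurrence and re-repair before month 9, no 1-year scan | Outcome scan missing, so the case falls under MAR imputation although the recurrence is known |

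The third and fourth rows are the problem.

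**Step 2: reproduce the planned sample size.** Inputs from Sample size {14}: 30% vs 10%, two-sided α 0.05 (the formula uses 1.96), power 80% (0.84), 1:1.

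n = [√(0.2 × 0.8 × 2) × 1.96 + √(0.3 × 0.7 + 0.1 × 0.9) × 0.84]² / 0.2² = [1.1087 + 0.4601]² / 0.04 = 61.53, so 62 per arm. The stated figure is right.

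Dropout: 124 / 0.85 = 146, and 150 × 0.85 = 127.5 evaluable, or about 64 per arm. The target of 150 covers the requirement.

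**Step 3: expected events.** 62 × 0.30 = 18.6 and 62 × 0.10 = 6.2, about 25 in total.

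**Step 4: illustrate the effect of reclassification.** Let r_C and r_G be the shares of control and gastropexy recurrences that are re-repaired before the scan and read as intact. These are assumptions, as the article gives no figure. The observed rates become 0.30(1 − r_C) and 0.10(1 − r_G).

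Exact power sums Bin(x; n, p₁) × Bin(y; n, p₂) over all (x, y) with |z| > 1.96, where z = [(x − y)/n] / √[2p̄(1 − p̄)/n] and p̄ = (x + y)/(2n). This is the unadjusted test behind the planning formula, used as a proxy for the adjusted logistic regression.

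| r_C, r_G | Observed rates | Difference | Power, 62 per arm | Power, 64 per arm |
|---|---|---|---|---|
| 0, 0 | 30% vs 10% | 20 points | 81.0% | 82.5% |
| 5%, 5% | 28.5% vs 9.5% | 19 points | 78.4% | 79.9% |
| 10%, 10% | 27% vs 9% | 18 points | 75.5% | 77.1% |
| 10%, 0 | 27% vs 10% | 17 points | 69.2% | – |
| 0, 10% | 30% vs 9% | 21 points | apparent benefit inflated | – |

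The normal approximation at 62 per arm agrees closely: 80.3%, 77.6%, 74.8% and 68.8% for the first four rows. At 10% in both arms the number reclassified is 18.6 × 0.1 + 6.2 × 0.1 = 2.48, or about 2.5 of 124 participants.

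**The case against.** **No sentence says such a participant is a success.** The definition of recurrence does not itself name which CT counts, and an analysis plan that is not shown could add a rule. This stands as a limit on wording: the scoring is a consequence of the text. But the article does fix the outcome at 1 year, set the window and restrict substitution to it, and following those statements gives the wrong classification.

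**The data are not lost.** A reader might infer that reoperations are collected only at 30 days and that later ones cannot be recovered. The text does not support that. It states a 30-day collection without saying it is the only one. Adverse event reporting {22} sends Clavien-Dindo ≥ 3b events to the safety committee with no stated time limit. Participants are contacted at 3 months, 1 year and 3 years, and medical records exist. None of these routes is linked to the endpoint, so a rule is still needed.

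**Imputation could use a recurrence documented before the scan.** The imputation model may include intermediate measurements, and a documented recurrence need not be treated as missing. That is possible, but the article does not say so.

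**The size is speculative.** This largely stands. The Discussion notes that many recurrences cause few or no symptoms, and the definition counts any part of the stomach, so early re-repair may be uncommon. Some re-repairs would themselves recur and be scored correctly. If the planning rate of 30% already came from scheduled scans, no planned power is lost. Evaluable numbers may be nearer 64 than 62 per arm.

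**A uniform scheduled CT has merit.** It ascertains both arms alike and is read blind. Surgeons are not among those listed as blinded under {17a}, so counting every clinically triggered CT would bring in symptom-driven ascertainment. This stands, and it is why the fix below is narrow.

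**Conclusion.** The point holds for recurrences re-repaired before the outcome scan, mainly before month 9. As written, the primary outcome scores these as no recurrence when the re-repair is intact, and leaves them to MAR imputation when the scan is missed. That does not answer the trial's question about the index repair.

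The size cannot be determined from the article. The illustrative range of 81.0% down to 75.5% power at 62 per arm (82.5% to 77.1% at 64) rests on three assumptions: a re-repair share of 0 to 10% equal in both arms, every re-repair intact on CT, and a 30% planning rate that counts re-repaired cases. With unequal shares the bias can go in either direction.

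A reader might go on to conclude that the trial is underpowered or biased against gastropexy. The documents support neither: the sample size reproduces and no re-repair rates are given. Nor is the absence of a stated rule for deaths an error here, since such detail is commonly left to the full protocol or analysis plan.

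**What to change.** Amend the outcome definition as follows:

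1. Score any participant reoperated for recurrent hiatal hernia before the 1-year outcome CT as a recurrence. Confirm it on the pre-reoperation CT, read by the blinded radiologist, or by the operative findings if there is no such CT.
2. Where a recurrence has been verified and no outcome scan follows, treat the outcome as observed and do not impute it.
3. Ascertain reoperations for recurrence at the existing 1- and 3-year contacts.
4. Apply the same rule to recurrence at 3 years.
5. Report the scheduled-CT-only definition as a sensitivity analysis.

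**Cost.** An amendment and a short question or chart check at contacts that already take place, with no extra scans or participants. There are two real downsides. Decisions to reoperate may be made by surgeons who know the allocation, so the added component is less protected than the blinded CT. The change also comes mid-trial: recruitment began in June 2023, so the first 1-year scans fell due around mid-2024. It should therefore be made and dated before any unblinded comparison. No interim analysis is planned and recruitment is expected to run to the end of 2026, so this appears feasible.
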